#### 2.1.6. Compliance and Adverse Effects

Compliance was assessed by instructing the participants to note/record any medication (new or not) intake and/or adverse events that might have happened during the course of the trial. We closely monitored the potential adverse events and, for this, we instructed the participants to immediately contact the research team in the case of unexpected medical care visits or serious adverse events/hospitalization. Reasons for discontinuation have been recorded.

#### 2.1.7. Primary and Secondary Endpoints

The primary endpoint was the change in the scores of the clinical IFI or SHARE-Fit scales from baseline to the T3, T9, and T15 trial period after treatment.

The secondary endpoint was the change in the molecular levels (RNA and proteins) from baseline over the T3, T9, and T15 trial period after treatment.

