## Abstract

Cognitive frailty (CF) is a heterogeneous syndrome that is becoming one of the most serious health problems as the world’s population age is increasing. Elucidating its biological mechanisms as well as prevention and treatments is becoming increasingly significant, particularly in view of the associated health costs. We presented the study protocol of a research project funded by the Italian Ministry of Health (grant number RF-2016-02363298) aiming to investigate the cognitive and neuropsychological effects of a 5-week treatment with therapy based on the regenerative properties of ozone (O_3_) in a cohort of subjects stratified according to CF scores. We also studied the potential effects of O_3_ on blood-based biomarkers indicative of specific biological systems that may be altered in CF. Seventy-five older persons were recruited and randomly assigned to receive the active treatment (150 cc of oxygen-O_2_-O_3_ mixture at the concentration of 30 µg of O_3_ per cc of O_2_), O_2_, or the placebo (air) for 5 weeks. The main endpoints were the change in the scores of clinical scales from baseline (T0) to weeks 3 (T3), 9 (T9), and 15 (T15) after treatment and the change in biomarker levels resulting from transcriptomics, proteomics, and metabolomic patterns at the same times. The positive results from this study could have important clinical implications.

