#### 2.1.5. Adaptive Randomization

Subjects were divided into three groups with different levels of cognitive frailty, defined according to tertiles of distribution of the scores of tests for the evaluation of memory skills (Story recall, Rey Auditory Verbal Learning Test—RAVLT immediate and delayed recall, and Rey–Osterrieth Complex Figure—ROCF Recall), attention skills (Trail Making Test part A and part B, TMT-A, TMT-B, Rey–Osterrieth Complex Figure—ROCF copy), and MMSE and GDS scores.

Participants were randomly assigned to the active treatment group (O_2_; O_2_-O_3_) or the placebo group (air), balanced for CF, so that each treatment arm accommodated a similar proportion of subjects in each tertile. The definition of the tertiles of CF was performed at different times, over a period of 12 months, on groups of 12/16 subjects, as enrollment progressed and before starting treatment. Being a double-blind study, both the researchers of the research team and the participants remained blinded to the treatment assignment until the completion of the study, while the medical doctor performing the treatment knew the treatment group, but not tertile of fragility. During recruitment, the medical doctor performing the treatment periodically re-evaluated the size of the treatment subgroups based on the recruitment and dropout rate.

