#### 2.2.2. Statistical Analysis

***Data analysis*.** We will present as means and standard deviations the descriptive statistics on cognitive and biological markers in the three treatment groups. The association between categorical variables will be analyzed using the Chi-square test.

The Automatic Linear Modeling (ALM) model that is based on a machine learning approach to find the best predictive model using available data will be used. A set of neuropsychological/biological values will be analyzed as independent input variables, while the scores of IFI or SHARE-FIt scales will be analyzed as continuous output (target) (dependent) variables. Longitudinal comparisons will be performed using univariate analysis, where the clinical parameters relating to the IFI and SHARE-FIt scales will be entered as dependent variables, the significant values obtained from ALM as covariates, and time and treatment as fixed factors. For the metabolomic analysis, PCA analysis (Principal Component Analysis) and a univariate analysis will be performed to evaluate the effects of the treatment on the presence/distribution of the metabolites. 

With the aim to correlate any clinical/cognitive improvements with molecular profiles to identify markers associated with response to treatment, the generalized linear mixed model (GLMM) will be used where the biological values and those relating to neuropsychological tests and the times of follow-up will be analyzed as independent input variables, while the values relating to the IFI or SHARE-FIt scales will be analyzed as weight variables and the treatments as (dependent) variables. “Air treatment” will be used as a comparison variable. All these analyses will be performed using SPSS ver. 29.

Differentially expressed genes will be identified using R-Bioconductor by applying both a fold change and p-value threshold (R-Limma test *p* value < 0.05; |Log2 fold-change ratio| > 1.0). By Fisher’s exact test, we will analyze the categories and functional pathways of upregulated or downregulated genes, using all genes in the array as the “reference” genome, or through the use of Ingenuity Pathway Analysis (IPA, Qiagen, Venlo, The Netherlands) to infer alterations in biological pathways and functions. 

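### The primary endpoint is either of two frailty scales at any of three visits in three arms; no primary scale or visit is fixed, and O2-O3 versus O2 is never named

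*Protocol article*

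**What the plan says.** - **Endpoint (protocol article, 2.1.7).** "The primary endpoint was the change in the scores of the clinical IFI or SHARE-Fit scales from baseline to the T3, T9, and T15". Change in RNA and protein levels is the secondary endpoint.
- **Arms (2.1.5).** "Participants were randomly assigned to the active treatment group (O_2_; O_2_-O_3_) or the placebo group (air), balanced for CF". The Abstract, 2.1.4 and 2.2.2 all describe three groups.
- **Longitudinal analysis (2.2.2).** A univariate analysis "where the clinical parameters relating to the IFI and SHARE-FIt scales will be entered as dependent variables", with "the significant values obtained from ALM as covariates, and time and treatment as fixed factors". Both scales are analysed. No visit, arm pair or reference arm is attached to this analysis.
- **Marker analysis (2.2.2).** A separate mixed model is meant "to correlate any clinical/cognitive improvements with molecular profiles to identify markers associated with response to treatment". After it comes the statement that air "will be used as a comparison variable".
- **Power (2.1.12).** 0.92 for IFI with 76 subjects and 0.80 for SHARE-FIt, each from a regression on neuropsychological tests.
- **Schedule (Table 1).** The row for clinical scales is ticked at baseline only.

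**The concern.** A primary endpoint should identify one result by which the trial will be judged. Here the word joining the two scales makes them alternatives, and the three visits have equal standing. This is not a slip of condensation: 2.1.12 gives separate power for each scale, and 2.2.2 carries both forward. Whichever scale, visit and arm pair looks best can be presented as the primary result, so the type I error of the trial's claim is not held at 5%.

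The rationale in the Introduction and Discussion is about ozone. A difference between O2-O3 and air could come from the oxygen; only O2-O3 versus O2 addresses ozone itself. Because that comparison is never named, a reader cannot tell whether the trial intends to test it.

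**Working it through.** **1. The plan's own figure.** The stated power (0.92 for IFI, 0.80 for SHARE-FIt) can be neither reproduced nor refuted, because 2.1.12 gives no R², number of predictors or alpha. For an overall F test with p fixed predictors, noncentrality N·R²/(1−R²), degrees of freedom p and N−p−1, N = 76 and an assumed alpha of 0.05:
- power 0.92 needs R² = 0.133 (1 predictor), 0.200 (5), 0.247 (10) or 0.320 (20);
- power 0.80 needs R² = 0.096, 0.154, 0.197 or 0.262.

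This is power for the link between cognitive tests and frailty scores. It is not power for a treatment comparison, so it does not show which comparison is primary.

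**2. Counting the tests.** Inputs are 2 scales and 3 visits (2.1.7) and 3 arms (Abstract, 2.1.5).
- One overall treatment test per scale, across visits: 2.
- Each gas arm against air, per scale and visit: 2 × 3 × 2 = 12.
- All three arm pairs, per scale and visit: 2 × 3 × 3 = 18, of which 2 × 3 × 1 = 6 are O2-O3 versus O2.

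**3. Chance of at least one false positive.** Assumption: two-sided 0.05 per test, each test valid at that level. If the tests were independent, the chance is 1 − 0.95^m:
- m = 2: 1 − 0.95² = 0.0975
- m = 12: 1 − 0.95¹² = 0.460
- m = 18: 1 − 0.95¹⁸ = 0.603

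The tests are correlated, because the scales overlap in content, visits repeat on the same people and arm pairs share an arm. The article gives no correlations, so ranges were assumed: 0 to 0.9 between scales and, for the per-visit tests, 0.3 to 0.9 between visits. Normal test statistics for three equal arms were simulated (200,000 draws per setting; 400,000 for the overall tests).

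| Reading | Tests | Independent | Correlated, range | Scale 0.5, visit 0.7 |
|---|---|---|---|---|
| Overall test per scale | 2 | 9.8% | 7.1–9.8% | 9.1% (scale 0.5) |
| Gas arms versus air, per visit | 12 | 46.0% | 20.2–41.6% | 32.4% |
| All pairs, per visit | 18 | 60.3% | 26.0–52.2% | 40.9% |

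**4. What fixing one test gives.** Assume 25 per arm (75/3; the article states no allocation ratio). The difference detectable with 80% power is (z for alpha + 0.84) × √(2/25):
- one test at 0.05: (1.96 + 0.84) × 0.283 = 0.79 SD;
- 12 co-primary tests under Bonferroni, 0.05/12 = 0.0042 each: (2.87 + 0.84) × 0.283 = 1.05 SD;
- 18 tests, 0.05/18 = 0.0028 each: (2.99 + 0.84) × 0.283 = 1.08 SD.

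Keeping every comparison and correcting for it would be expensive at this sample size. Choosing one avoids that loss.

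**The case against.** The strongest reply is that contrasts, alpha and a testing hierarchy are commonly left to an analysis plan, which is not shown, and that the Discussion calls the trial a pilot whose results need confirmation in a larger population. The first part stands for alpha and hierarchy: their absence is not the finding. It does not rescue 2.1.7, where the endpoint itself is stated as a choice. The pilot label lowers the confirmatory weight, but it does not say which result is primary.

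Four stronger readings are tempting, and the article does not support them.

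- *At least 12 primary comparisons.* Twelve is not a minimum. It needs separate tests at each visit, which 2.2.2 does not describe; time and treatment as factors can equally mean one treatment test per scale, hence 2.
- *O2-O3 versus O2 is excluded.* The sentence making air the comparator follows the marker model, not the longitudinal comparison of the scales. If no contrast is fixed, O2-O3 versus O2 is one of those left open. It is unnamed, not ruled out.
- *The two gas arms will be pooled.* Section 2.1.5 labels both as active, but the Abstract, 2.1.4 and 2.2.2 keep three groups and no pooled analysis is described. Any loss of power from pooling is hypothetical.
- *The Abstract makes biomarkers primary.* It begins "The main endpoints were the change in the scores of clinical scales" and goes on to biomarkers. That phrase can cover primary and secondary endpoints together, and 2.1.7 and the Discussion both call biomarkers secondary. This is a minor wording point.

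**Conclusion.** The concern holds in this form: the primary endpoint fixes neither scale nor visit, and the comparison specific to ozone is never named. The false-positive risk for the trial's claim is above 5% on every reading: about 7–10% on the most favourable one, 20–42% with 12 correlated tests and 26–52% with 18. These sizes rest on an assumed two-sided 5% per test and on assumed correlations. The article does not say which reading applies, so no single figure can be given. Even the most favourable reading leaves the choice of scale open and does not show which arms differ.

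**What to change.** Before treatment codes are opened:

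1. Name one primary scale (for example IFI, which has the higher stated power), one time point or summary (T15, or the average over T3 to T15) and one contrast (for example O2-O3 versus air), tested at two-sided 5%.
2. Test the rest in fixed sequence: O2-O3 versus O2 on the same endpoint, then SHARE-FIt. Require the O2-O3 versus O2 step to succeed before any effect is attributed to ozone.
3. Report other visits, and O2 versus air, descriptively with confidence intervals.
4. State that the three arms are analysed separately, and call biomarkers secondary in the Abstract too.
5. Reconcile Table 1 with 2.1.7. If IFI and SHARE-FIt belong to the clinical-scales row, the table shows no follow-up scores for the primary endpoint. Reconcile the visit units as well: the Abstract gives weeks, while 2.1.4 and Table 1 give months.

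Section 2.1.5 says the research team stays blinded until completion, but the Discussion reports analyses under way and Data Availability says raw data are deposited. The sponsor should state whether codes are still closed. If they are open, the choice must be reported as post hoc.

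The change to the plan is wording only and needs no extra participants. The price is that SHARE-FIt, or a result at a single unselected visit, can no longer carry the claim alone. If follow-up frailty scores were not collected as 2.1.7 implies, the choice of primary is limited to what exists.

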#### 2.2.1. Molecular Analyses

Blood sample material will be used to perform transcriptomic, proteomic, and metabolomic studies.

***Proteomic analyses*.** We plan to perform a cytokines and growth factors panel to be analyzed through automated the ELISA Platform (Bioplex, Biorad, Hercules, CA, USA).

***Mass spectrometry***.

**UHPLC–QqTOF–MS analysis.** Serum metabolic profiling analysis will be conducted using a UHPLC–MS system with a Bruker compact QqTOF MS (Bruker Daltonics, Billerica, MA, USA) and a Dionex UltiMate 3000 Rapid Separation LC (Thermo Fisher Scientific, Waltham, MA, USA) equipped with an Acquity UPLC BEH C18 (300 Å, 2.1 × 150 mm, 1.7 μm) column (Waters). MS parameters will be set up using microToF 3.4, ESI Compass 1.3, and HyStarPP 3.2 SR4 software (Bruker Daltonics, Billerica, MA, USA). A 10 µL aliquot of samples will be injected into the HPLC column, and elution will be performed at a flow rate of 0.4 mL/min using a gradient elution program as follows: 0 min, 5% B; 2 min, 5% B; 7 min, 40% B; 9 min, 80% B; 9.1 min, 100% B; 14 min, 100% B; 14.1 min, 5% B; 20 min, 5% B. The column temperature will be set up at 60 °C. The total running time will be 20.1 min. Mobile phase A will consist of 0.1% CH2O2 (formic acid) in H_2_O, while mobile phase B will consist of 96% EtOH. Ionization will be performed using an electrospray ionization (ESI) source, operating in positive mode. ESI source conditions will be set up as follows: capillary voltage, 4.0 kV; dry gas (N2) flow, 8.0 L min^−1^; dry gas (N2) temperature, 300 °C; nebulizer pressure, 3.0 bar. The mass scan range will be set from 200 to 950 *m*/*z*. The instrument will be calibrated prior to the analyses using 10 mM sodium formate.

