The secondary endpoint of the trial is the change in biological markers levels in terms of proteomics, transcriptomics, and metabolomics. As the syndrome is multidimensional, the identification of biomarkers in CF is a complex process. In the context of the neuroimaging field, several recent papers agreed that CF is associated with loss of structure in specific brain regions such as the thalamus and hippocampus, as well as changes in white matter hyperintensity [43]. At the metabolic level, a longitudinal study performed in a population of 7769 individuals included in the Doetinchem Cohort Study [44] evidenced that markers such as high-density lipoproteins, triglycerides, alanine aminotransferase, gamma-glutamyltransferase, albumin, uric acid, cystatin C, and creatinine were not predictive of CF. Contrarily, Royal and Plamen [45] observed that the levels of insulin-like growth factor 1 and IGF-binding protein 2 levels were found to be altered in patients with cognitive decline and physical frailty. Moreover, Sargent et al. [46] reported lower levels of vitamin E alpha tocopherol, omega-6 and 3, and albumin in subjects with CF. In addition, the same authors found a further significant association with lower levels of low- and high-density lipoproteins. Finally, the focus on microbiota is a new further aspect in the development of new age-related biomarkers. For instance, He et al. [47] demonstrated that CF patients showed elevated levels of trimethylamine N-oxide, a stable metabolite of the intestinal microbiota.

In this study, we will apply a high-throughput -omic approach that will allow us to analyze the whole transcriptome and proteome in order to identify potential known as well as new biomarkers associated with the response to O_2_-O_3_ therapy treatment and, consequently, new therapeutic targets for O_3_. We thus expect that O_3_ can potentially influence biological systems linked to the immune–inflammatory system, the stress response, and oxidative stress, regeneration processes which are altered in the CF. In particular, those genes that will be differentially expressed before and after treatment and that thus will be modulated by the therapy will be verified at the biochemical level along with a panel of proteins (proteomics) that will include cytokines (i.e., IL-1β, IL-6, TNFα), immune factors (i.e., MCP-1, RANTES, MIP1), and growth factors (i.e., VEGF, BDNF, NGFβ).

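### Protein change is part of the secondary endpoint, but no stated model has a protein as its outcome, and the model relating proteins to arm does not estimate the treatment effect

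*Protocol article*

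**What the plan says.** Section 2.1.7 defines the endpoint: "The secondary endpoint was the change in the molecular levels (RNA and proteins) from baseline". The visits it names are T3, T9 and T15. The Discussion (section 3) restates it more widely: "The secondary endpoint of the trial is the change in biological markers levels in terms of proteomics, transcriptomics, and metabolomics". Proteins belong to it under both statements.

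Section 2.2.1 describes how the proteins are assayed: "We plan to perform a cytokines and growth factors panel to be analyzed through automated the ELISA Platform". It attaches no statistical model to them.

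Section 2.2.2 describes the statistical analysis. Proteins are not named there, but they fall under its biological values and markers:

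- Descriptively: "We will present as means and standard deviations the descriptive statistics on cognitive and biological markers in the three treatment groups".
- In the ALM, which has IFI or SHARE-FIt as target: "A set of neuropsychological/biological values will be analyzed as independent input variables".
- In the longitudinal comparison, "the clinical parameters relating to the IFI and SHARE-FIt scales will be entered as dependent variables". Values found significant by the ALM are covariates; time and treatment are the factors.
- In the GLMM, biological values are inputs, together with the neuropsychological tests and follow-up times. IFI or SHARE-FIt are weights, treatment is the dependent variable, and air is the comparison.

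Metabolites are given PCA and a univariate analysis of the effect of treatment. Genes are given a limma differential-expression analysis with stated thresholds.

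**The concern.** An endpoint defined as change from baseline needs an analysis in which that change, or the follow-up level given baseline, is the outcome and treatment is the explanatory term. Section 2.2.2 supplies such a structure for the frailty scales and names an outcome analysis for metabolites and for genes. For proteins it places the measurement on the explanatory side throughout.

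If the section is followed as written, the report would contain protein means and SDs by arm and a set of GLMM coefficients. Neither is an estimate, with an interval, of how much O2-O3 or O2 changed a protein relative to air. The risk is that the GLMM coefficients are read as that estimate. They answer a different question, and with correlated proteins they can show nothing, or the wrong direction, where treatment had a real effect.

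**Working it through.** The article states no figure on this point, so there is none to reproduce. The check has two steps.

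**Step 1: the role of proteins in each analysis of section 2.2.2**

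| Analysis | Dependent variable | Role of proteins |
|---|---|---|
| Descriptive statistics | none | means and SDs by arm |
| ALM | IFI or SHARE-FIt | input |
| Longitudinal univariate model | IFI and SHARE-FIt | covariate, if the ALM selects it |
| PCA and univariate analysis | metabolites | none |
| GLMM | treatment arm | input |
| Limma | gene expression | none |

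Proteins are the dependent variable in 0 of these. The only stated model that links proteins to arm is the GLMM.

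**Step 2: can the GLMM stand in for a treatment effect on a protein?**

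Consider one active arm against air and two markers, each with SD 1 and correlation r in both arms. Let d1 and d2 be the true treatment effects on the markers, in SD units. If the markers are normal with equal covariance in the two arms, a logistic model with arm as the dependent variable has coefficients b = Σ⁻¹d, that is

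- b1 = (d1 − r·d2) / (1 − r²)
- b2 = (d2 − r·d1) / (1 − r²)

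The documents give no protein effects or correlations. The values of r, d1 and d2 below are assumptions for illustration.

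- r = 0, d = (0.80, 0.48): b = (0.80, 0.48). The coefficients match the effects.
- r = 0.6, d = (0.80, 0.48): b1 = (0.80 − 0.288)/0.64 = 0.80; b2 = (0.48 − 0.48)/0.64 = 0.00. A real effect of 0.48 SD on the second marker disappears.
- r = 0.6, d = (0.80, 0.80): b1 = b2 = (0.80 − 0.48)/0.64 = 0.50. Two equal effects are both shrunk.
- r = 0.8, d = (0.80, 0.40): b1 = (0.80 − 0.32)/0.36 = 1.33; b2 = (0.40 − 0.64)/0.36 = −0.67. The sign of the second effect reverses.

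A simulated logistic fit of the second case, with 200,000 per arm, gave 0.800 and −0.003, in agreement with the formula.

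The illustration leaves out the IFI/SHARE-FIt weights, the third arm, the neuropsychological inputs and the repeated visits. The first of these would make the coefficients depend on the frailty scores as well. None of them would turn the coefficients into estimates of change in a protein.

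**The case against.** The strongest objection is that this is a condensed article. Section 2.1.2 refers to a full protocol, version 3.0, which is not shown, and an analysis plan may exist. The model for a biomarker panel is often left to such documents, and section 2.2.2 nowhere says that proteins will not be tested as outcomes. This would dispose of a complaint about silence. It does not dispose of this one: section 2.2.2 lists its models with their dependent variables, provides outcome analyses for the other data types, and fixes the one model linking proteins to arm in the reversed direction.

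Three stronger readings are tempting, and the documents do not support them.

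- A reader might infer that the plan gives no information at all on treatment and proteins. The GLMM does give a protein-arm association against air, and arm means allow a crude comparison. What is missing is a direct estimate of the treatment effect on protein change.
- A reader might infer that metabolites are analysed although they lie outside the endpoint, while proteins, half of it, are not. That follows section 2.1.7 alone. The Discussion includes metabolomics in the secondary endpoint, and the Abstract also lists metabolomic patterns among the endpoints.
- A reader might infer from the Discussion that the protein panel is meant as independent proof of the gene findings, because modulated genes "will be verified at the biochemical level along with a panel of proteins". The wording sets the panel beside the verification, in forward-looking prose, and claims no independent replication.

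Counts of false-positive protein tests would not measure this problem either, because no such tests are planned. It also stands that the Discussion calls the trial a pilot and says that its results should be confirmed in a larger population, which limits the weight of the point.

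**Conclusion.** The concern holds in limited form. Change in protein levels over T3, T9 and T15 is part of the secondary endpoint under either statement of it, and proteins are the outcome in none of the models in section 2.2.2. The GLMM is not a substitute. Its coefficients are conditional on all other inputs and weighted by the frailty scales. In the illustration they take a true 0.48 SD effect to 0.00 (correlation 0.6) and turn a true 0.40 SD effect into a coefficient of −0.67 (correlation 0.8).

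The first conclusion rests on the text alone. The second rests on the normal, equal-covariance illustration with assumed effects and correlations. It shows what can happen and does not predict what will happen in this trial; with uncorrelated markers the distortion would be absent. The change should be made, but the point concerns a secondary endpoint and leaves the primary analysis untouched.

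**What to change.** Add to section 2.2.2 an analysis with each panel protein as the outcome, and name it the analysis of the protein part of the secondary endpoint. One suitable form is a mixed model for the protein level, on a suitable scale, at T3, T9 and T15, with the T0 value, arm, visit, arm-by-visit and a person effect. Report each active arm against air with an interval, and O2-O3 against O2 if that contrast is wanted. Control the false-discovery rate across the panel. Other models with the protein as outcome and baseline taken into account would also serve.

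Keep the GLMM for its stated aim of finding markers of response, label it exploratory, and say that its coefficients are not treatment effects on proteins.

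The cost is a paragraph and a few extra models. The blood samples at T0, T3, T9 and T15 are already part of the schedule, and section 2.2.1 lists the panel as still to be run, so no new data are needed. The small downside is that fewer proteins will be called changed after error control.
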